**23.**
* Bilateral ocular application of pupil dilator medication Minims Tropicamide 1.0%:* Application of pupil dilator solution will take place on Study Day 2 approximately 30 minutes prior to the light stimulation protocol

**24.**
* 30 minute light pulse*: Participants will be exposed to a 30 minute light pulse on Study Day 2. The light stimulation will be delivered 90 minutes prior to the estimated core body temperature nadir.

**25.**
* Follow-up wellbeing call:* For participant wellbeing to ensure no experiences of significant manic or depressive symptoms occurred due to the study protocol. The follow-up assessment will consist of a telephone call from the clinical research fellow on the team within 3 days of the completion of Study Day 2.

**3.7.1.3
Part B
**

**26.**
* Cone-isolating chromatic thresholds*, measured using the Cambridge Colour Test. Participants observe Landolt Cs and indicate their orientation. Their responses feed into a staircase that controls stimulus contrast until a threshold is accurately measured.

**27.**
* Contrast sensitivity functions*. Participants observe gratings of different spatial orientations and indicate their orientation. Their responses feed into a staircase that controls stimulus contrast until a threshold is accurately measured.

**28.**
* Just noticeable differences for colour and luminance-defined stimuli* (blue, orange and luminance-defined). Participants observe two patches and indicate which one is brighter, redder or bluer. Their responses feed into a staircase that controls stimulus contrast until a threshold is accurately measured.

**29.**
* Pupillary responses*. Participants are presented with lights that differentially stimulate melanopsin and chromatic pathways and their pupillary response is measured using a RetinaWise device from Oculowise (Switzerland).

**30.**
* Visual evoked potentials to spatiochromatically modulated stimuli*. Participants will observe a series of bipolar Gabor patches defined along blue-yellow, red-green or achromatic dimensions at several levels of contrast - from low contrast to contrast matching the maximum achievable chromatic modulation within the gamut of our screen. To control attention, participants will be asked to respond to a rare orientation oddball Gabor stimulus, whilst refraining from responding to all other stimuli.

**3.7.1.5
Part C
**

**31.**
* Fundus camera photograph*. A fundus camera generates a 2D, high resolution image showing the optic disc, macula and blood vessels, and permits analysis of these anatomical features.

**32.**
* Ultra-widefield scanning laser ophthalmoscopy*. An ultra-widefield scanning laser ophthalmoscope (UWF-SLO) captures 80% of the retina in an image.

**33.**
* Optical coherence tomography (OCT).* OCT images the retinal nerve fibre layers (RNFL) and inner layers of the retina.

**34.**
* OCT Angiography (OCT-A)*. OCT-A reveals the very small capillary level vessels in the retina which are not possible to image in any other way.

**35.**
* Optical biometry*. Optical biometry yields the eye’s axial length - i.e. the distance from front to the back - a vital measure used to account for differences in individuals’ eyes and an important metric for the evaluation of retinal biomarkers.

**36.**
* Automated perimetry*. Automated perimetry tests a participant’s visual field.

**37.**
* Autorefraction*. Autorefraction measures a participant’s refractive error (i.e. how short- or long-sighted they are).

**
*3.7.2 Storage and analysis of samples*
**

Blood samples will be collected as part of the Part A protocol detailed in
Section 3.2.4. A maximum of 31 blood samples will be collected in total as part of the study protocol. Control and BD Non-Lithium groups will have 30 samples collected. The ‘bipolar disorder on lithium’ group will have an additional sample collected to test lithium levels.

Sample collection

In the first instance, as noted above, one 2ml blood sample (‘bipolar disorder on lithium’ group only) and one 8ml blood sample will be taken during Part A. The 2ml sample will be used for lithium level analysis, and will be sent immediately for processing by the laboratory at the Royal Infirmary of Edinburgh. The 8ml sample will be processed and stored long-term at -80 degrees in University of Edinburgh facilities (The Institute of Genetics and Cancer, Western General Hospital) until use in future ethically approved research.

As described above, a total of 29 blood samples will be collected between the hours of 7pm and 6am across both Part A study nights for melatonin level analysis.

Sample storage

Blood samples for melatonin analysis will be centrifuged for plasma extraction and stored in freezers at -80C in the Clinical Research Facility, Royal Infirmary of Edinburgh. Samples will be stored according to the participant (i.e. all samples from one participant will be stored together in 1 box).

Blood samples for long-term storage (and future use in ethically approved studies) will be stored long-term at -80 degrees in University of Edinburgh facilities (The Institute of Genetics and Cancer, Western General Hospital) until use.

Sample processing

1 sample for lithium level analysis will be processed by the biochemistry laboratory at Royal Infirmary of Edinburgh. 1 sample for future ethically approved research (e.g. retinal organoid work (HELIOS-BD Workstream 1) which will be processed by our collaborators [name] and [name] in Newcastle/Northumbria, subject to approvals). 29 samples for melatonin level analysis will be processed and analysed by NovoLytix GmbH, Switzerland. Samples will be analysed in patient batches to control for assay variance. Surplus sample from the analysis process will be destroyed.

### 3.8 Data collection

**
*3.8.1 Source data documentation*
**

Source data is defined as all information in original records and certified copies of original records or clinical findings, observations, or other activities in a clinical study necessary for the reconstruction and evaluation of the study. Source data are contained in source documents. Source documents are original documents, data and records where source data are recorded for the first time.

**3.8.1.1
Paper source documents
**

•     Consent forms

•     Sleep diary

**3.8.1.2
Digital source documents
**

•     Consent form

•     Electronic Case Report Form - includes procedural checklists and the following data collection instruments:

◦ Personal data and contact details◦ Screening data (inclusion/exclusion criteria)◦ Retrospective Assessment of the Lithium Response Phenotype (Alda) Scale score (standardised questionnaire of lithium response phenotype)◦ Alcohol Use Disorders Identification Test (AUDIT) score (standardised questionnaire of alcohol use)◦ Lifestyle information (standardised questionnaire)◦ Past psychiatric history (standardised questionnaire)◦ Medication history (standardised questionnaire)◦ Pittsburgh Sleep Quality Index (PSQI) score (standardised questionnaire of sleep quality)◦ Munich Chronotype Questionnaire (MCTQ) (standardised questionnaire of chronotype)◦ Modified Seasonal Pattern Assessment Questionnaire (m-SPAQ) (standardised questionnaire of seasonality)◦ WHODAS 2.0 Questionnaire score (standardised questionnaire of health and disability)

•     Blood sample analysis (melatonin levels)

•     Actigraphy data (electronic data collection) for 12 days prior to & including overnight CRF stays

•     Ambient light level data (electronic data collection) for 12 days prior to & including overnight CRF stays

•     Core Body Temperature (electronic data collection)

•     Psychophysical data: all psychophysical result files will contain single trial data indicating response accuracy at each stimulus level. Data will be stored as .txt files, to ensure compatibility.

•     Pupilometry: pupil size will be digitally recorded for each light exposure setting and stored in an open-source digital format.

•     Electroencephalography: Data will be recorded in Biosemi format but processed and stored using the default data format of the EEGlab toolbox for Matlab, which is a gold standard in digital EEG data processing.

**
*3.8.2 Case report forms*
**

The Case Report Forms are electronic and hosted on the Research Electronic Data Capture (REDCap) server software (
https://www.project-redcap.org/; RRID:SCR_003445) (
Harris *et al.*, 2009;
Harris *et al.*, 2019). The REDCap software is accessed via a web application which allows users to enter and store data in a secure and intuitive user-friendly system. It is used around the world to securely gather research data.

 REDCap server software will be accessed using internet browsers on local University of Edinburgh network computers based in Kennedy Tower, University of Edinburgh laptops, remotely via the University of Edinburgh VPN and NHS Lothian computers located at the Clinical Research Facility, Royal Infirmary of Edinburgh. Only members of the research team will be able to register for a password-protected REDCap user account and have access to the study project on the server. Data will be extracted from the electronic CRFs as password-protected, encrypted excel spreadsheets, which will be stored on the University of Edinburgh DataStore, accessed via University of Edinburgh network computers based in the Division of Psychiatry, Kennedy Tower, Royal Edinburgh Hospital (University of Edinburgh).

### 3.9 Data management

**
*3.9.1 Data storage and access*
**

**3.9.1.1
Paper data
**

All identifiable paper records (e.g. signed consent forms) will be stored in a locked filing cabinet in a locked office at the Kennedy Tower, Royal Edinburgh Hospital (University of Edinburgh). Only the research team members will have access to this, which includes investigators and collaborating groups who have been approved by the study investigators. University of Edinburgh policy regarding data management will be followed at all times (
https://www.ed.ac.uk/information-services/about/policies-and-regulations/research-data-policy). Following completion of the research project, identifiable paper records will be destroyed after 12 months.

**3.9.1.2
Digital data
**

Screening & baseline visit

Digital identifiable data will be stored on secure REDCap server software and will be accessible for the duration of the study. The REDCap instance used for this study is run by Clinical Surgery, University of Edinburgh within the University of Edinburgh Virtual Machine architecture. It is physically secured (servers are physically located at the King’s Buildings campus, The University of Edinburgh, [name], UK). All transmission and storage of web-based information by this online system is encrypted and was designed to be compliant with HIPAA-Security Guidelines.

Part A

Digital data from the eCelsius telemetric pill will be transmitted wirelessly to the eCelsius monitor in the CRF, and data from this will then be securely downloaded from the eCelsius monitor to the study computer at the Clinical Research Facility, via a direct USB connection. This data will be stored in a .csv spreadsheet, which will in turn be uploaded to the participant’s corresponding REDCap electronic CRF and downloaded to the University of Edinburgh study DataStore (controlled by Information Services at University of Edinburgh). Only authorised members of the research team will have access to the data store.

Digital data from the ActLumus light logger will be securely downloaded to a study computer at the Clinical Research Facility, via a direct USB connection. This data will be stored in a .csv spreadsheet, which will in turn be uploaded to the participant’s corresponding REDCap electronic CRF.

The NHS Lothian medical records of enrolled participants with bipolar disorder will be accessed by the study team to access any information relevant to the study, i.e., that entered at the Clinical Research facility and lithium levels, and then entered into the participant’s REDCap electronic CRF and downloaded to the study DataStore.

Digital data from the AX3 actigraph will be securely downloaded to a University of Edinburgh secure server, via a direct USB connection. This data will be stored in a .cwa file on the study DataStore.

After completion of each participant’s participation in the study, their electronic CRF data will be exported from the REDCap server and fileswithin an encrypted password protected folder on the study DataStore. Upon study completion all data stored using REDCap will therefore have been exported for processing and analysis purposes. All data will be deleted from REDCap 1 year after study completion.

Part B

Digital data from psychometric testing and EEG will be stored electronically in pseudonymised form in a secure folder on DataStore (controlled by Information Services at University of Edinburgh). Only authorized members of the research team will have access.

Part C

Digital data from retinal imaging will be stored electronically in pseudonymised form in a secure folder on DataStore (controlled by Information Services at University of Edinburgh). Only authorized members of the research team will have access.

All study data

Data held on the DataStore will be pseudonymised and the principles of data minimisation will always be followed. Only members of the research team will be able to access the data held on the DataStore, using a secure username and password. Any data which includes personal or identifiable information will additionally be encrypted and password protected.

Data .csv files will be accompanied by meta-data prepared in accordance with UK Data Service and Data Documentation Initiative guidelines. Documentation will include: a data dictionary (.csv file with rows for each variable and columns for: variable label, variable description, variable response scale codes, including missing data codes); a technical report that includes further background information on each variable (organised according to scales and subscales), including processing and further references; a study protocol detailing study design and data collection, with copies of all assessments and questionnaires annotated with variable labels included as appendices.

Personal data will be stored for 15 years after study completion on the University of Edinburgh DataVault. For one year following study completion, data will be held in pseudonymised format. After deletion of identifiable data (one year after study completion), the study dataset will effectively become anonymised. Anonymised digital data will be kept for a period of 14 years after the deletion of identifiable data.

No data will be shared out with the research team without explicit participant consent via the participant consent form. Anonymised data will be made available for download in line with open access principles. Anonymised data will be available for download via an Open Science Framework (OSF) project (
osf.io). This data will be available to the wider research community no later than 1 year after the completion of the project.

We will ensure published data (i.e. in academic manuscripts) does not contain any information that could disclose participant identity. Published results will be a descriptive analysis of aggregate results.

**3.9.1.3
Blood sample data
**

For the melatonin level analysis, the samples will be sent from University of Edinburgh to NovoLytiX GmbH ([name]) and then extracted and measured with the NovoLytiX Melatonin RIA (RK-MEL2). They will be sent in a pseudonymised format, with the only identifier being the participant ID number. The results from this analysis will be entered into the Excel files sent in advance by a member of the research team to NovoLytiX GmbH, and subsequently sent back to the research team after completion of each batch of measurements. The raw data are archived anonymously at NovoLytiX GmbH and can be accessed by the principal investigators or other authorised third parties at any time during office hours (after prior registration).

For the lithium level analysis (BD on Lithium group only), results will be stored on the NHS TRAK database and will be linked to the participant’s CHI number. Only NHS staff will have access to these data.

**
*3.9.2 Transfer of data*
**

No data will be shared without explicit participant consent via the participant consent form. Participants will be asked for their GP and psychiatrist’s name, and for consent to inform them that they are taking part in the study, and of any notifiable results. This information will be posted or emailed securely to the GP.

**
*3.9.3 Data controller*
**

The joint data controllers are the University of Edinburgh and NHS Lothian.

**
*3.9.4 Data breaches*
**

Any data breaches will be reported to the University of Edinburgh (
[contact]) and NHS Lothian (
[contact]) Data Protection Officers who will onward report to the relevant authority according to the appropriate timelines if required.

### 3.10 Outcome measures

**
*3.10.1 Primary outcome measures*
**

**3.10.1.1
Part A
**

Difference in absolute change in plasma melatonin levels in response to light stimulation protocol between the 3 study groups.

**3.10.1.2
Part B
**

Difference in pupillometry, visual evoked potential, and chromatic discrimination/detection measures between the 3 study groups.

**3.10.1.3
Part C
**

Retinal structure differences between the 3 groups assessed over time

**
*3.10.2 Secondary outcome measures*
**

**3.10.2.1
Part A
**

To determine absolute differences in the following measures between the 3 study groups:

ALDA scale (Bipolar Disorder groups only)PSQI total score for sleep qualityMCTQ total score for chronotypeMEQ total score for chronotypeWHODAS 2.0 total score for global functionm-SPAQ total score for seasonal sensitivity

**3.10.2.2
Part B
**

Correlation of primary outcome measures with other, non-retinal measures acquired in the study (e.g. questionnaires, medical history), as well as with each other.

**3.10.2.3
Part C
**

Secondary outcomes include cross-sectional and longitudinal differences in retinal vascular metrics; retinal layer thickness; small vessel metrics; eye biometrics; visual field metrics. These outcomes will be correlated with other, non-retinal measures acquired in the study.

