### 2.4 A potential mechanism of action for lithium

Lithium has been in clinical use for over 70 years and is acknowledged to be the most effective long-term treatment for bipolar disorder. In the UK, the National Institute for Health and Clinical Excellence recommends lithium as a first-line treatment for bipolar disorder. However, lithium has variable efficacy within the bipolar disorder population, with roughly one third of individuals having a ‘full’ response. Lithium has many reported actions – including modulation of monoamine neurotransmission (
Ferrier *et al.*, 2006), inhibition of glycogen synthase kinase-3 (
Klein & Melton, 1996), reducing the hyperexcitability of neurons and neuroprotection (
Mertens *et al.*, 2015) – but the precise mechanism of action in bipolar disorder remains an active area of research. Given the considerable etiological and clinical heterogeneity of bipolar disorder, it is possible that lithium has different modes of action within different patient subgroups.

Central to this protocol is convergent evidence suggesting that lithium may work (at least in a proportion of patients) by stabilising aberrant circadian rhythms of mood, cognition and rest/activity. Animal studies demonstrate that lithium reduces light-induced phase delays (
Duncan *et al.*, 1998) and that it modulates the pupillary response to light (
Seggie *et al.*, 1989). In humans, 5 days of lithium ingestion was shown to significantly decrease melatonin suppression in healthy volunteers, with no significant effect on nocturnal melatonin secretion overall (
Hallam *et al*. 2005). Additionally, human MRI research showing that lithium accumulates in the eye (
Smith *et al*., 2018). Taken together, it is plausible that lithium’s circadian-regulating effects occur via an action at the level of the retina to reduce light sensitivity and non-visual response to light. If lithium were to normalise aberrant retinal signalling in some way, this may also reduce bipolar-specific visual responses to light. Further, sustained lithium use might be neuroprotective, preventing or attenuating progressive structural retinal changes.

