### 3.6 Study population

**
*3.6.1 Sample size calculation*
**

This study will assess 180 participants:

*n*=60 with bipolar disorder and currently on lithium therapy
*n*=60 with bipolar disorder and not taking lithium
*n*=60 healthy controls with no history of mental illness and no first-degree family history of mental illness

The required sample size for this study is calculated from melatonin measures relevant to Part A. This sample size is sufficient for both Part B and Part C of the project (see below). Sex and gender differences were not taken into consideration in study design or sample size calculations because there is no conclusive evidence of sex or gender differences in the primary study outcome measures.

**3.6.1.1
Part A Sample Size Calculation
**

Our subjects of interest are BD patients versus controls, with the BD group sub-divided into two groups: one where BD subjects are on lithium therapy and another where BD subjects are not taking lithium. Based on previous reports of light-induced melatonin suppression in BD (
Hallam *et al.*, 2009) we expect a difference of approximately 40–50% (Cohen’s d effect size 0.5–0.6) between the BD lithium group and the BD non-lithium group. As such, for 80% power with an alpha of 5%, we will need 42 participants in each of the three groups. Allowing for incomplete data collection in up 30% of participants, this means that we will recruit 60 participants in each group.

**3.6.1.2
Part B Sample Size Calculation
**

With this sample size (N=180 participants across three groups), a two-sided between-subjects t-test at 80% power with an alpha level of 0.05 will be able to reliably detect an effect size of d=>0.52, equivalent to a difference of 0.52 of a standard deviation (i.e., medium effect size). Comparably, a between-subject ANOVA with three groups would be able to detect an effect size of f=>0.23. For a clinical study of this kind, this represents a very high level of sensitivity. As a minimum, it will allow us to provide a more definitive characterisation of the observed phenomena than previous studies in this field. As a comparison, studies with groups of 20 participants, which are common in the existing literature, are capable of detecting an effect of d=>0.9 (two groups) or f=>0.41 (three groups), which are large effect sizes.

**3.6.1.3
Part C Sample Size Calculation
**

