**BD Lithium participant group**

Participants in the ‘BD Lithium’ group must have a diagnosis of bipolar disorder according to DSM V criteria, confirmed with the Structured Clinical Interview for DSM5 (SCID) with at least one previous manic or two previous hypomanic episodes. Where possible, the diagnosis of bipolar disorder will be corroborated using clinical notes or records. Participants in the ‘BD Lithium’ group must be clinically euthymic with no episodes of depression, hypomania or mania for at least three months prior to enrolment. Participants will be asked to inform the study team of any mood episodes they have developed in the three months prior to any study appointment. Affected appointments will be rescheduled once the participant has been euthymic for 3 months. They must be on a stable lithium medication regimen for at least six months prior to study participation.

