**BD Non-Lithium participant group**

Participants in the ‘BD Non-Lithium’ group must have a diagnosis of bipolar disorder according to DSM V criteria, confirmed with the Structured Clinical Interview for DSM5 (SCID) with at least one previous manic or two previous hypomanic episodes. Where possible, the diagnosis of bipolar disorder will be corroborated using clinical notes or records. Participants in the ‘BD Non-Lithium’ group must be clinically euthymic with no episodes of depression, hypomania or mania for at least three months prior to enrolment. Participants will be asked to inform the study team of any mood episodes they have developed in the three months prior to any study appointment. Affected appointments will be rescheduled once the participant has been euthymic for 3 months.

Participants in the ‘BD Non-Lithium’ group must not be currently taking lithium, and must have no lithium use for at least six months prior to study participation.

**
*3.6.3 Exclusion criteria*
**

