* Collection of contact details*: Contact details will be collected during the initial screening appointment to allow for further communications between the research team and potential participants.

**2.**
* Verbal informed consent*: Potential participants will provide verbal informed consent for the purposes of the screening call data collection.

**3.**
* Assessment of eligibility criteria*: Potential participants will be screened for eligibility criteria at the initial screening day and again at baseline study visit. This will include a structured diagnostic assessment for bipolar disorder at the screening appointment.

**3.7.1.2
 Baseline study visit
**

**4.**
* Written informed consent*: Potential participants who meet the study eligibility criteria will provide written informed consent during enrolment to the study at baseline study visit.

**5**
* Demographic and lifestyle data (self-reported)*: Age; self-reported sex; gender identity, ethnicity; educational attainment; employment status; socioeconomic status measured using the Townsend Deprivation Index; smoking status.

**6.**
* Alcohol Use Disorders Identification Test, AUDIT (Saunders
*et al*., 1993)*: Validated questionnaire to assess alcohol use.

**7.**
* Past psychiatric history*: Data including age of onset, number and timing of episodes of depression, hypomania and mania will be collected. This is to gain a full understanding of the participant’s clinical history.

**8.**
* Assessment of past and present medication use*: To be used as variates in future analyses.

**9.**
* Retrospective Assessment of the Lithium Response Phenotype (Alda) Scale (
Grof *et al*., 2002)*: Validated questionnaire to retrospectively assess lithium response phenotypes in bipolar disorder participants.

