### 3.11 Statistical analysis

**
*3.11.1 Proposed analyses*
**

**3.11.1.1
Part A analyses
**

We will compute the area under the curve for the melatonin profile using the trapezoidal method and also compute the percentage difference between the healthy control group and the BD lithium therapy group, as well as between the healthy control group and the BD non-lithium treatment group. We will then use one-way ANOVA (or Kruskal-Wallis) with post-hoc analyses (Tukey) across the three groups, as well as undertaking general linear model analyses controlling for potential confounding variables such as age, sex, ethnicity, educational attainment, employment status, socioeconomic status, smoking status, alcohol use, sleep quality, chronotype, psychiatric history, medication use and score on the Alda lithium response scale. 

**3.11.1.2
Part B analyses
**

Statistical analyses for the various measures (pupillary response, colour perception, spatiochromatic processing, visual evoked potentials) across the three groups will be performed using linear mixed effect models with healthy control group set as the baseline (i.e., zero) level for all the comparisons. Models will also be evaluated for the contribution of confounding factors, including age, sex, ethnicity, educational attainment, employment status, socioeconomic status, smoking status, alcohol use, sleep quality, chronotype, psychiatric history and medication use and score on the Alda lithium response scale.

**3.11.1.3
Part C analyses
**

We will test the hypothesis that people with BD have significant differences in structural and functional measures of the retina and in the trajectory of change compared to controls. Additionally, we will assess whether individuals with BD who are taking lithium have an attenuated trajectory of change compared to those with BD on other medications. Student’s t-test and generalised estimation equations will be used to examine differences in retinal measures and psychophysical thresholds between the three participant groups. Spearman’s rank correlation coefficient will be used to investigate associations of retinal measures and psychophysical thresholds with other key parameters from the study data, including confounding demographic and clinical factors. Trajectory analysis will be used to assess changes in retinal parameters and psychophysical thresholds over time and how effective this approach is at stratifying participants.

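### The Alda lithium-response score is a between-group secondary outcome, but it is undefined for never-users of lithium and otherwise compares people who continued lithium with people who stopped

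*Protocol article*

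**What the plan says.** All references are to the protocol article.

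- **Outcome (3.10.2.1).** The Part A secondary outcomes open with "To determine absolute differences in the following measures between the 3 study groups". The first measure listed is "ALDA scale (Bipolar Disorder groups only". Controls are set aside and both bipolar groups are kept, so the comparison is BD Lithium against BD Non-Lithium.
- **What the scale is (3.7.1.2, item 9).** "Validated questionnaire to retrospectively assess lithium response phenotypes in bipolar disorder participants".
- **BD Non-Lithium group (3.6.1 and 3.6.2).** Sixty participants "with bipolar disorder and not taking lithium". They "must not be currently taking lithium, and must have no lithium use for at least six months prior to study participation". Past lithium use is neither required nor excluded.
- **BD Lithium group (3.6.2).** "They must be on a stable lithium medication regimen for at least six months prior to study participation".
- **Analysis (3.11.1.1 and 3.11.1.2).** The list of potential confounders for the Part A general linear models and the Part B mixed models ends with "medication use and score on the Alda lithium response scale". The Part B models use the healthy controls as the reference level.
- **Background (2.4).** Lithium efficacy is described as variable, with "roughly one third of individuals having a" full response.

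**The concern.** A rating of response to a drug presupposes that the person took the drug. The entry criteria allow some of the Non-Lithium group never to have done so, and for them the outcome has no value. The others in that group took lithium and stopped. The groups are thus defined by whether lithium is being continued, and the outcome is how well lithium worked. If people tend to stay on a drug that helps them, a difference in Alda score follows from the way the groups were formed and says little about either group's biology.

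Two things are at stake. The first is a secondary outcome that could show a clear difference and be read as a finding. The second is the use of the score as a covariate in models that include controls and never-users. Those rows would either be dropped or be given an arbitrary value, and neither serves the comparison with controls.

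**Working it through.** The plan gives no sample size, effect or power for the Alda comparison, so there is no figure of its own to reproduce. The check has three steps.

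**1. Who can be scored.** Inputs: 60 per group (3.6.1); share *q* of never-users in the Non-Lithium group, not given and therefore assumed. Scorable n = 60 × (1 − *q*). The detectable standardised difference against 60 lithium users (two-sided 5%, 80% power, t-test) is roughly 2.80 × √(1/60 + 1/n); the exact t-test values are shown.

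| Assumed *q* | Scorable n | Detectable d |
|---|---|---|
| 0% | 60 | 0.52 |
| 25% | 45 | 0.56 |
| 50% | 30 | 0.63 |
| 75% | 15 | 0.82 |

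The first row agrees with the 0.52 that section 3.6.1.2 quotes for groups of this size. The lower rows show only that precision depends on a share nobody has stated.

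**2. What the contrast measures among those who can be scored.** Inputs: full-response share p = 1/3 (2.4), applied here to everyone who ever took lithium, which is itself an assumption; probability of staying on lithium *a* for full responders and *b* for others, neither given.

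- Full responders among continuers = p*a* / [p*a* + (1 − p)*b*]
- Full responders among stoppers = p(1 − *a*) / [p(1 − *a*) + (1 − p)(1 − *b*)]

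With *a* = 0.7 and *b* = 0.5:

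- continuers: 0.2333 / (0.2333 + 0.3333) = 41%
- stoppers: 0.1000 / (0.1000 + 0.3333) = 23%

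| Assumed *a* / *b* | Continuers | Stoppers |
|---|---|---|
| 0.5 / 0.5 | 33% | 33% |
| 0.7 / 0.5 | 41% | 23% |
| 0.8 / 0.4 | 50% | 14% |
| 0.9 / 0.3 | 60% | 7% |

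Swapping the second row (*a* = 0.5, *b* = 0.7) reverses the sign: 0.1667 / (0.1667 + 0.4667) = 26% of continuers against 0.1667 / (0.1667 + 0.2000) = 45% of stoppers. So the contrast can be large, nil or reversed according to continuation behaviour alone, with no other difference between the groups.

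**3. The covariate use.** Section 3.10.2.1 itself confines the scale to the bipolar groups, so all 60 controls lack a score, as does every never-user. A three-group model with Alda as a covariate and complete-case handling would lose every control and could no longer estimate the contrast with controls. Filling in a constant would make the coefficient depend on the constant chosen.

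**The case against.** The strongest reply is that this is one of six Part A secondary measures, mostly questionnaires that characterise non-randomised groups. A condensed article may also leave the handling of never-users to a data dictionary or analysis plan; section 3.9.1.2 promises a dictionary with missing-data codes and a technical report on processing. That stands as far as it goes: the absence of a coding rule is not the fault. But no coding rule rescues the comparison. Setting never-users to missing leaves continuers against stoppers, and giving them a number makes one up.

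It can also be said that part of the remedy is already present, since sections 3.10.2.2 and 3.10.2.3 correlate Part B and Part C outcomes with other study measures. That is fair, and it makes the change easier. It does not remove the between-group outcome or the covariate.

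A reader might infer more than the documents support, in three ways:

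- **That the entry criteria fix the direction, because ex-users are poor responders.** No criterion mentions lithium response, and no reasons for stopping are given. Some people may stop for tolerability. Equal continuation gives no difference at all.
- **That euthymia adds to the imbalance.** Section 3.6.2 requires three months of euthymia in both bipolar groups, so it is not part of the problem.
- **That never-users would be scored as non-responders.** The article proposes nothing of the kind.

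**Conclusion.** The point holds as a minor one. Two parts rest on the text alone: the between-group Alda outcome is undefined for any never-users, whom the criteria admit, and among the remaining participants it sets continuers against stoppers. The same lack of a score affects the covariate lists in sections 3.11.1.1 and 3.11.1.2.

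That the contrast mainly reflects who stays on lithium is likely but not established. Its direction and size depend on three things the documents do not give: the share of never-users, the continuation rates, and whether one third full responders applies to everyone in this sample who ever took lithium. The 41% against 23% is an illustration and not an estimate.

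The primary outcome definitions and the Part A sample size, which is based on melatonin, are not affected.

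**What to change.** - **3.10.2.1:** remove the Alda scale from the list of between-group outcomes. Use it among lithium-exposed participants, mainly within the BD Lithium group, as a predictor of melatonin, pupil and retinal response. That asks whether better lithium responders show less light response, which bears on the study's own hypothesis about lithium.
- **Non-Lithium group:** describe ex-users' scores separately and record never-users as not applicable.
- **3.11.1.1 and 3.11.1.2:** take the Alda score out of the three-group covariate lists and confine it to the within-lithium analysis.

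This is a rewording of one outcome line and two covariate lists. It needs no new data or visits, and it can be done before analysis because the study is still recruiting. The cost is one secondary between-group comparison. The predictor analysis also rests mainly on a single group of at most 60, so it will be less precise than a full-sample analysis.
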